### Project management and participant tracking

We developed an official WeChat account, and create 30 WeChat group. All parents of children download the app (WeChat) free of charge and create a unique identifying username.

Before the intervention starts, each WeChat team will be allocated a project staff from the study team. Under the direct leadership of the project director, project staffs will be responsible for:1) tracking team members to ensure that all necessary data are collected in a timely fashion; 2) providing timely and relevant feedback to the study team; and 3) sending education materials to the WeChat team.

### Statistical analyses

Descriptive statistics will be calculated using mean (SD) for continuous variables and n (%) for categorical variables. Differences will be compared using independent t-tests for continuous variables (e.g., blood sample outcomes) and Chi-squared tests for categorial variables (e.g., education and household income of parents). Linear mixed models will be used to test for group differences on the main outcome variables at follow-up visits, while subject ID will be random effect, the main effect include time, treatment group, and the interaction between time and treatment. We will include covariates that are not balanced between two groups into the model. Data will be entered and cleaned with EpiData 3.0, and managed and analyzed using SPSS 24.0 and SAS. Statistical significance will be set at *P* < 0.05.

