### Sample size consideration

Based on the relative studies on exercise intervention with obese children [29], the sample size required for each group was estimated to be about 175 with a power of 80%, an α of 0.05, and assumed an effect size of 0.30. Therefore, a total of 350 children are need. To account for 20% loss-to-follow-up, a total of 420 children will be recruited.

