### Social incentive intervention design

Previous research has found that a combination of individuals and teams could increase participants’ engagement [33]. Peer support, accountability and team discussion also has been proved to enhance social incentives [34]. Thus the intervention will add these features to promote enduring involvement:Grouping: In order to enhance social incentives, WeChat groups are established respectively for the intervention group and the control group by the investigators. The intervention group will be divided into 30 teams involving 6–7 members according to BMI, age and sex. Because a pilot study has showed that one group within 5–6 members had the best partner interaction [35].A kick-off meeting: After randomization, a kick-off meeting will be organized by the investigators and all participants in the intervention group will be asked to attend. In the meeting, the investigators will introduce the intervention protocol and ensure teammates fully understand what they need to do. Then, each team will perform several interactions to foster familiarity and cohesion among their teammates, as well as elect their team leader. A kick-off meeting can increase effective and positive interaction in social groups and promote engagement as well as motivation [36].Daily Report within Teams: Parents urge the children to skip rope every day and report the daily information (include: data recorded by Actigraph wGT3X-BT; ‘whether the number of rope skipping reach the standard’) to their team WeChat group before 22:30 PM on the day.Peer Support: Each day teammates (the family who represent child) develop at least one interaction in the WeChat group. Praising teammates who reach the standard and encourage those who don’t reach (e.g., ‘Doing well and keep going.’) are also required. Criticism and ridicule, which might cause negative reactions, are not allowed.Accountability: Team leader responsibility system is implemented in the group. The team leader is responsible for reminding their members to complete daily task and send “PS” (the abbreviation of peer support). The team leader rotates once every month for fairness.Team discussion: Healthy tips will be posted by the study team in each group every Friday. Participants will be guided to read it and communicate with teammate on their gains as well as barriers of the program.

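### The intervention is delivered in 30 interacting teams, but the mixed model has no team term and the 175 per group assumes independent children; the effect is small at an intra-team correlation of 0.02 and material from about 0.05

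*Protocol article*

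**What the plan says.** **Delivery.** The section Social incentive intervention design says "The intervention group will be divided into 30 teams involving" six to seven children each. It requires daily interaction among teammates, a rotating leader who reminds members of their tasks, and team discussion. Gamification intervention design adds team rankings, rewards and weekend competitions. Under Project management and participant tracking, "each WeChat team will be allocated a project staff from the study team". Controls do not receive the package. A WeChat group is set up for the control group, but no small teams are described for it.

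**Analysis.** Statistical analyses specifies linear mixed models in which "subject ID will be random effect, the main effect include time, treatment group, and the interaction between time and treatment". No team term appears. The other comparison named for continuous variables is the independent t-test, which also assumes independent children.

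**Sample size.** Sample size consideration states that "the sample size required for each group was estimated to be about 175", using 80% power, "an α of 0.05, and assumed an effect size of 0.30". The evaluable total is 350, raised to 420 for 20% loss. No ICC or design effect is mentioned.

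**The concern.** A child random effect accounts for repeated visits by the same child. It does nothing for correlation between different children in one team. The intervention is designed to work through mutual influence, and each team also shares a leader and a staff member, so positive correlation within teams is to be expected. Because only one arm is clustered, the design is partially nested.

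If that correlation is left out, the standard error of the group comparison is too small. Confidence intervals are then too narrow, the test of the primary metabolic outcomes rejects too often when there is no effect, and the power calculation promises more than a correctly specified analysis would deliver.

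**Working it through.** **Inputs from the article:** 175 evaluable per group; two-group comparison; α 0.05 (sidedness not stated; two-sided reproduces the figure); effect size 0.30, read as a standardised mean difference; 420 recruited, so 210 per arm; 30 teams in the intervention arm. Allocation is read as allocation of individual children after consent.

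**Assumed:** ICC 0 to 0.10, because the documents give none; equal total variance in both arms; normal approximation; a single cross-sectional comparison.

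**Step 1: reproduce the stated figure.** n per arm = 2 × ((1.96 + 0.842) / 0.30)² = 174.4, rounded up to 175. Power at 175 per arm: SE = √(2/175) = 0.1069, and Φ(0.30/0.1069 − 1.96) = 80.1%. A one-sided test would need 138. The stated 175 is therefore the two-sided figure for independent children.

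**Step 2: allow for teams in the intervention arm only.** Evaluable team size m = 175/30 = 5.83.

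- Design effect: DE = 1 + (m − 1) × ICC
- True SE = √(DE/175 + 1/175); naive SE = √(2/175)
- Power of a correctly specified test = Φ(0.30/true SE − 1.96)
- Type I error of the naive test = 2 × (1 − Φ(1.96 × naive SE/true SE))
- n per arm for 80% power = (DE + 1) × ((1.96 + 0.842)/0.30)², with m held at 5.83

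Example at ICC 0.05: DE = 1 + 4.83 × 0.05 = 1.242; true SE = √(2.242/175) = 0.1132; power = Φ(2.65 − 1.96) = 75.5%.

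| Assumed ICC | DE | True/naive SE | Power | Naive type I error | n per arm for 80% |
|---|---|---|---|---|---|
| 0 | 1.000 | 1.000 | 80.1% | 5.0% | 175 |
| 0.02 | 1.097 | 1.024 | 78.3% | 5.6% | 183 |
| 0.05 | 1.242 | 1.059 | 75.5% | 6.4% | 196 |
| 0.10 | 1.483 | 1.114 | 71.2% | 7.9% | 217 |

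**Step 3: separate the loss allowance.** 420 = 350 × 1.2, whereas 350/0.8 = 437.5, or 438. Losing 20% of 420 leaves 336, or 168 per arm. With no clustering, power there is Φ(0.30/√(2/168) − 1.96) = 78.5%. With m = 168/30 = 5.6, ICCs of 0.02, 0.05 and 0.10 give 76.7%, 74.0% and 69.8%. The first 1.5 or so points below 80% come from the loss arithmetic, not from teams.

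**Step 4: which team term corrects the planned contrast.** The model contains a time-by-treatment interaction. Take 30 teams of 7 (210 per arm), with assumed variances of child 0.5, residual 0.5 and team 0.1. For the change from baseline to one follow-up visit:

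- Child effects and a time-constant team intercept both cancel, so SE = √(2 × 2 × 0.5/210) = 0.0976 with or without that intercept.
- A team effect present only after baseline does not cancel. SE = √(0.00952 + 0.1/30) = 0.113.

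Teams are formed after randomisation, so the second case is the relevant one if baseline is among the modelled visits.

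**The case against.** **The ICC is unknown.** This stands. The primary outcomes are blood indices and blood pressure, whereas teams act on reporting and exercise, so correlation in the outcomes could be weak. At 0.02 the loss is under 2 points of power and the type I error is 5.6%. Nothing in the article supports one value over another.

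**The article is a condensed account and an analysis plan may say more.** This does not remove the point. The article itself fixes the random effect and the basis of the sample size, and both conflict with the delivery that it describes.

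**The power formula is not that of the planned test.** This stands. A repeated-measures model depends on the within-child correlation, which is not given. The figures show the cost of clustering on the same basis as the plan's own calculation.

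Three stronger readings are tempting and not supported:

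- A reader might infer that 80% power holds only if the ICC is zero. After the planned loss, power is 78.5% even at zero. With no loss at all (210 per arm, 7 per team), it is still 81.8% at an ICC of 0.05.
- A reader might pair a type I error of 8.6% at an ICC of 0.10 with the power after dropout. That error figure belongs to teams of 7, the top of the stated range, before any loss. At 5.6 per team it is 7.7%.
- A reader might infer that forming teams by BMI, age and sex inflates the variance. Sorting children who are already randomised does not by itself change the variance of the arm comparison, and the article does not say whether teams are to be alike or balanced on these factors. The case rests on interaction and on shared leaders and staff.

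**Conclusion.** The concern holds as an inconsistency between delivery and analysis. It should be fixed before analysis, but it does not show that the trial is invalid or that more children must be recruited. The direction is firm for any positive intra-team correlation: standard errors are too small, and power at 175 evaluable per arm is below the stated 80%. The size is uncertain because it depends on an ICC that the documents do not give. On the basis used here, the effect is small at 0.02 and material from about 0.05. At 0.10 the naive SE is about 10% too small (1/1.114 = 0.90) and power is about 9 points lower. This rests on individual allocation, equal total variance in both arms, a single follow-up comparison and no small-sample degrees-of-freedom correction. The shortfall from the loss allowance is a separate matter and should not be attributed to teams.

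**What to change.** 1. Record each intervention child's team at the kick-off meeting as an analysis variable.
2. Fit a partially nested model: a team random effect in the intervention arm only, with each control child as a singleton, and Satterthwaite or Kenward-Roger degrees of freedom.
3. State how baseline enters the model and match the team term to it. If baseline is one of the modelled visits, the team effect must act on post-baseline visits, since a time-constant intercept leaves the change contrast uncorrected. If baseline is a covariate and only follow-up visits are modelled, a team intercept suffices.
4. Adjust for baseline BMI, age and sex, so that similarity created by forming teams on these factors is not counted as a team effect.
5. Restate power at 420 children over a declared ICC range, including zero, and show the effect of the loss allowance separately.

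The cost is a few lines of model specification and one added variable, with no change to recruitment or conduct. SAS, already named in the plan, fits such models. The downside is slightly wider intervals and a less favourable stated power.

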### Randomization

The study will use stratified random sampling, and the random sequence of primary schools will be computer generated. Specifically, it stratified by school district, grades and size in each center. All of the children in the selected primary schools of different grades were invited to participate in the study.

After both parents and children written informed consent have been obtained, it will be allocated into either an intervention or control group in a 1:1 ratio. Neither the study team nor the participant knew the group allocation prior to the start of the intervention program.

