### Intervention

We used WeChat as the social media platform to carry out the intervention. A WeChat group is created for each group by the investigators. The intervention group will receive skipping rope plus the ‘gamification exercise package’. Data will be collected five times: at baseline, at end of intervention period, in the follow-up time at months 3,6,12.

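### Model covariates are to be chosen by observed imbalance between the arms, with no stated criterion, instead of being fixed in advance with the baseline outcome value among them

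*Protocol article*

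**What the plan says.** All wording on the model stands in the protocol article, Statistical analyses.

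- Model and target: "Linear mixed models will be used to test for group differences on the main outcome variables at follow-up visits".
- Terms always present: "the main effect include time, treatment group, and the interaction between time and treatment", and "subject ID will be random effect".
- The only covariate rule: "We will include covariates that are not balanced between two groups into the model".
- Group comparisons: "Differences will be compared using independent t-tests for continuous variables", with chi-squared tests for categorical variables. The examples given are blood results and parental education and income. The section does not say that these tests decide what counts as unbalanced.

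No threshold for imbalance and no list of candidate covariates is given. The baseline outcome value is available, because the Intervention section says: "Data will be collected five times: at baseline, at end of intervention period". The Randomization section also mentions design factors: "it stratified by school district, grades and size in each center".

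**The concern.** A covariate earns its place in a randomised comparison by predicting the outcome. A difference between arms at baseline is a chance event and carries no information on that. A rule keyed to imbalance can therefore admit variables with no prognostic value and leave out strong predictors. The child's own baseline value of an index is usually the strongest predictor available, and it is already measured.

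Two things are at stake. The first is precision that costs nothing to obtain. The second is that the primary model is fixed only after the data have been inspected, by a criterion the document does not define. Two analysts could follow the same sentence and fit different models. This is not a detail left to a fuller document: the article states a selection rule, and an analysis plan that followed it would inherit the weakness.

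**Working it through.** **Inputs from the protocol article.** Effect size 0.30 (SD taken as 1), power 80%, α 0.05, 175 per group (Sample size consideration); 1:1 allocation (Randomization); baseline plus four later assessments (Intervention).

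**Assumptions not in the document.** Correlation ρ between baseline and follow-up value of 0.3, 0.5 and 0.7; imbalance declared when a baseline t-test gives p<0.05; two-sided testing; one follow-up visit; individually randomised, independent children.

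**1. The plan's own figure.** n per arm = 2(1.96 + 0.8416)² / 0.30² = 2 × 7.849 / 0.09 = 174.4, so 175. Power at 175 per arm = Φ(0.30 × √(175/2) − 1.96) = Φ(0.846) = 80.1%. The stated size reproduces as an unadjusted two-sided comparison; a one-sided test would need 138.

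**2. Always adjusting for baseline.** The residual SD is √(1 − ρ²), so power = Φ(0.30 × √87.5 / √(1 − ρ²) − 1.96), and n for 80% power is 174.4 × (1 − ρ²).

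| ρ | Power, 175 per arm | n per arm for 80% |
|---|---|---|
| 0.3 | 83.7% | 159 |
| 0.5 | 90.0% | 131 |
| 0.7 | 97.6% | 89 |

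**3. The imbalance rule, if only follow-up visits are modelled.** Simulation of 20,000 trials per setting, 175 per arm, adjusting for baseline only when its t-test has p<0.05, which happens in about 5% of trials.

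| ρ | Power, rule | Power, always adjust | Loss (points) | Type I error, rule |
|---|---|---|---|---|
| 0.3 | 80.1% | 83.3% | 3 | 4.5% |
| 0.5 | 80.9% | 89.5% | 9 | 4.2% |
| 0.7 | 81.5% | 97.4% | 16 | 3.5% |

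**4. If baseline is a level of time.** The treatment effect is then a difference in change. Its variance is proportional to 2(1 − ρ), against 1 − ρ² for baseline adjustment, so the ratio is 2(1 − ρ)/(1 − ρ²) = 2/(1 + ρ): 1.54, 1.33 and 1.18. Power of the change contrast at 175 per arm is 66.0%, 80.1% and 95.2%, against 83.7%, 90.0% and 97.6% with adjustment.

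**5. How much the undefined criterion leaves open.** With an effect of 0.30, the adjusted and unadjusted tests disagree on significance in 6.8%, 12.5% and 18.5% of simulated trials. With no effect, they disagree in 2.80%, 4.78% and 6.59%. The chance that at least one is significant is half the sum of the two rejection rates and the disagreement rate:

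- ρ = 0.3: (4.70 + 4.81 + 2.80)/2 = 6.2%
- ρ = 0.5: (4.97 + 4.98 + 4.78)/2 = 7.4%
- ρ = 0.7: (4.96 + 4.84 + 6.59)/2 = 8.2%

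This is the ceiling if an analyst could choose freely between the two, not the error rate of the written rule. If 8 to 10 independent covariates were screened at 0.05, the chance of flagging at least one is 1 − 0.95⁸ = 34% to 1 − 0.95¹⁰ = 40%.

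**The case against.** The strongest reply is that the rule may never touch the baseline outcome value. If baseline is one of the levels of time, it is in the model as a response, and the covariates in question are background variables such as parental education. The text does not settle this; the reference to follow-up visits leans the other way. On this reading the power losses in step 3 do not apply. What stands is step 4: the change contrast is less precise than baseline adjustment. That loss comes from how baseline enters the model, not from the imbalance sentence, which would still govern every other covariate.

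The size is also uncertain. The document gives neither ρ nor the trigger, and at ρ = 0.3 the gain is only about 3 points.

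Some stronger conclusions that a reader might draw are not supported:

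- *The rule inflates false positives.* Applied mechanically it is slightly conservative (step 3). Only the discretion left by the missing criterion could push the error up.
- *Stratification factors are balanced by design and so are always dropped.* The Randomization section attaches the strata to the sampling of schools and does not clearly say that allocation of children was stratified.
- *Imbalance will be judged by the t-tests and chi-squared tests.* This is plausible, but the section does not make the link.
- *Each primary index will get its own model.* That would arise mainly if each index's own baseline value were screened, which the text does not say. Screening background variables would give one common set.

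**Conclusion.** The concern holds in a limited form. The document states a poor selection rule with no criterion, and nowhere fixes the baseline outcome value as a covariate. Under either reading of the model, precision is given away: about 3 to 16 points of power if only follow-up visits are modelled, or a variance 1.54 to 1.18 times that of baseline adjustment if baseline is a level of time. Both ranges are for ρ from 0.3 to 0.7. The first also rests on the assumed p<0.05 trigger, and both on individual allocation and one follow-up visit.

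It would go too far to say that the nominal error rate is breached or that the primary result would be invalid. Randomisation still protects the comparison, and the demonstrated harm is lost precision plus avoidable room for choice. This should be fixed; it is a free improvement and not a condition for the trial's validity.

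**What to change.** Replace the covariate sentence with a set named in advance:

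- the baseline value of the outcome being analysed, or a longitudinal model that includes baseline as a response and constrains the two arms' baseline means to be equal;
- age and sex;
- grade;
- school, where children are allocated individually within schools. The Randomization section leaves the unit of allocation unclear. If whole schools were allocated, fixed school terms would be aliased with treatment, so the unit must be stated first.

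State explicitly whether baseline is a covariate or a level of time. Drop imbalance as a selection rule and keep any adjustment for observed imbalance as a labelled sensitivity analysis.

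The cost is a few lines in the statistical section. It needs no new measurement, visit or participant: outcomes are already measured at baseline, age and sex are already used to form the intervention teams, and school and grade are known from recruitment. The change should be dated before outcome data are examined.

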## Discussion

An novel exercise intervention (‘S&G exercise intervention’) with WeChat as support, based on social incentives and gamification design, as well as ensuring intensity and dose of exercise, may have potential to improve metabolic health and even change unhealthy behaviors for long-term. In a randomized controlled trial design, the present study will assess the effectiveness of a ‘S&G exercise intervention’ to improve metabolic health and unhealthy behaviors.

The prevalence and severity of childhood obesity and metabolic abnormality in worldwide have increased [1, 31], which may lead to CVD and type 2 diabetes in adulthood [9, 10]. How to address it becomes an important demand worldwide. At present, several randomized controlled studies has proved that supervised exercise can improve metabolic risk factors, but once the supervised exercise is stopped, the health benefits weaken or vanish, and the exercise interventions also suffer from high-cost and small scale [46]. Remarkably, recent researches have suggested that social incentive and gamification were used in health interventions and have a potential effect on long-term maintenance [25, 47]. Moreover, WeChat also can provide an appropriate platform to deploy interventions on a broader, low-cost scale. Therefore, providing low cost, scalable and the long-term effective interventions to reduce metabolic risks among obese children becomes available.

To our knowledge, ‘S&G exercise intervention ’ was the first time to be designed, which make up traditional supervised exercise (SE) intervention limitation, and it can increase engagement as well as sustain exercise interventions effects on low cost, larger scale. Moreover, this study is not only targeted the effect of reduction of health outcomes including obesity and metabolic disorder, but also focused on healthy behavior changes including daily PA, diet pattern, sleep health and screen media use, which are significantly associated with health behaviors and health status in their adulthood. Hence, this study can also make a significant contribution to health research and practice by developing a new intervention model to promote unhealthy behaviors among obese children.

We predicted that this innovative exercise intervention (‘S&G exercise intervention package’) will develop improvements in metabolic health and unhealthy behaviors among obese children. We believed that this study could explore a low-cost, easy-to-popularize, and effective exercise intervention model for improving metabolic health and promote healthy among obese children. Furthermore, it will also provide important evidence for guidelines to prevent and improve metabolic health and health behaviors.

